**Fig. 1 Fig1:**
[figure not shown]
The CONSORT flow diagram. EG, experimental group; CG, control group; white boxes indicate procedures common to both groups; grey boxes indicate group-specific procedures

### Procedure

#### Screening

Prospective participants initially complete the PRPSA-18 through a custom-developed webpage to assess their PSA levels and undergo additional online self-screening. Participants meeting inclusion criteria with scores of 58 points or higher receive detailed study information and are invited to the laboratory for in-person eligibility confirmation. During screening, participants are also assessed for exclusion criteria including current diagnosis of severe mental illness, ongoing psychiatric treatment, or presence of suicidal ideation (defined as scoring ≥ 1 on item 9 of the PHQ-9). Individuals meeting any exclusion criteria are not eligible for study participation.

At the laboratory visit, a study investigator confirms eligibility, explains the study, and obtains written informed consent. Participants are then enrolled and randomized to the experimental or control group in a 1:1 ratio using computer-generated allocation. Baseline assessment (T0) is conducted after randomization and before the first intervention session. To minimize noise potentially affecting physiological indicator measurements, participants are advised to maintain adequate sleep and limit caffeine and alcohol consumption during the 1-week period from study enrollment through intervention completion. This lifestyle management serves to enhance measurement accuracy of physiological indicators related to autonomic nervous system function.

#### Pre-session voice recording and stabilization before each session

Participants receive brief study explanations before donning Head-Mounted Displays (HMD) and physiological monitoring equipment (Shimmer3 GSR + unit; Shimmer Sensing, Dublin, Ireland). Following equipment setup, participants produce 1) a 5-s sustained vowel/a/(“ah ~ ”; the central 3 s analyzed) and 2) a continuous reading passage from the standardized Korean paragraph “Fall” (Kim, 1996; see Appendix A for full text, IPA transcription, and English translation), which provides balanced phonemic coverage and is widely used for voice and speech assessments [36]. These recordings will be analyzed for fundamental frequency (F0), intensity, pause duration, and speech rate as baseline prosodic indicators. The sustained vowel duration aligns with CAPE-V recommendations for stable phonation [37]. The passage length was selected to ensure sufficient voiced material for reliable acoustic and temporal analyses, as long-term speaking-rate measures typically stabilize within ~8–16 s [38].

After the voice recording, participants undergo a 3-min stabilization period during which they fixate on a small black dot displayed at the center of a blank VR screen. This stabilization phase allows physiological indicators to reach baseline levels and facilitates adaptation to the VR environment. The interview simulation then proceeds automatically. At Session 1, these measures form part of the study baseline assessment (T0); analogous pre-session recordings in Sessions 2 and 3 are used only for within-session standardization and are not additional baseline assessments.

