**Fig. 4 Fig4:**
[figure not shown]
SPIRIT schedule of enrollment, interventions, and assessments throughout the study timeline. Timepoints are designated as follows: -T1 (online self-screening, in-person eligibility confirmation at the laboratory, written informed consent and randomization), T0 (baseline assessment), T1–T3 (immediate post-session assessments during the three VR intervention sessions), T4 (6-week follow-up), and T5 (12-week follow-up). The intervention phase (T1–T3) includes both experimental group (graded interviewer reactions) and control group (automated prompts) protocols. Primary outcomes (PSAS, LSAS-SR, FNE-B) are measured at all six timepoints, while physiological indicators (PPG, GSR) and behavioral measures (movement, voice data) are collected only during the intervention sessions (T1–T3). X marks indicate when each assessment or procedure is conducted

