#### Data preparation and planned analyses

Missing participant data are included in analyses for intention-to-treat (ITT) analysis. ITT analysis preserves randomization principles while reflecting actual clinical environments, analyzing all randomly allocated participants according to their original group assignments regardless of dropout or protocol violations [51]. Primary and secondary analyses of self-report questionnaires outcomes will be conducted using linear mixed-effects models, with fixed effects for group, assessment occasion, and their interaction, and participant-specific random effects to account for within-subject correlation across repeated measurements.

PPG data undergo preprocessing using third-order Savitzky-Golay filters, with heart rate variability analyzed in the time domain to capture short-term autonomic responses. Primary analyses compare PPG-derived, time-domain HRV and heart rate measures between groups during key intervention phases (interviewer questioning, presentation, and stabilization) to assess short-term autonomic reactivity. The primary outcome is ΔRMSSD (presentation minus baseline stabilization), representing parasympathetic reactivity. Secondary analyses include comparisons of mean HR, ΔHR, SDNN, and pNN50 to capture overall autonomic activation and variability. Long-term habituation patterns will be examined by modeling within-subject slopes of ΔRMSSD and ΔHR across the three sessions, with an anticipated progressive reduction in reactivity in the experimental group.

GSR signals are decomposed into tonic (SCL) and phasic (SCR) components using Continuous Decomposition Analysis [48, 52]. For between-group comparisons, phasic response magnitude to interviewer questions are analyzed across sessions. Tonic arousal levels are compared between groups throughout the entire intervention period. Within the experimental group, GSR responses across the sequential positive, neutral, and negative interviewer-reaction stages will be explored in relation to concurrent self-report and behavioral anxiety indicators. Because these stages are delivered in a fixed sequence as part of a single graded intervention package, these analyses will be interpreted as exploratory and will not be used to infer the independent causal effect of each reaction valence.

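### The Session 1 stabilization is defined as T0 baseline, yet the analysis section compares it between groups as a phase of the intervention

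*Protocol article*

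**What the plan says.** Under Pre-session voice recording and stabilization before each session, participants make a voice recording and then look at a dot on a blank screen for three minutes. The purpose is given as "This stabilization phase allows physiological indicators to reach baseline levels and facilitates adaptation to the VR environment". Only afterwards does exposure start: "The interview simulation then proceeds automatically". The section then fixes the status of these data: "At Session 1, these measures form part of the study baseline assessment (T0"). For the later visits, "analogous pre-session recordings in Sessions 2 and 3 are used only for within-session standardization and are not additional baseline assessments".

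Under Data preparation and planned analyses, the plan is to compare heart rate and time-domain HRV "measures between groups during key intervention phases (interviewer questioning, presentation, and stabilization"), with short-term autonomic reactivity as the stated aim. No session is excepted. The same paragraph names ΔRMSSD, the presentation value less the resting value, as the main physiological outcome. It adds: "Secondary analyses include comparisons of mean HR, ΔHR, SDNN, and pNN50". Habituation is to be studied through participant-level slopes of ΔRMSSD and ΔHR over the three sessions.

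Under Secondary outcomes, RMSSD, SDNN, pNN50 and the skin-conductance variables are to be compared between groups over the stages of the intervention. The Fig. 4 caption says that physiological data "are collected only during the intervention sessions (T1–T3").

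**The concern.** One measurement has two roles. In the procedure section the Session 1 stabilization is a pre-exposure baseline. In the analysis section stabilization stands beside questioning and presentation as a phase in which the arms are compared.

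A difference between arms before any arm-specific content cannot be caused by interviewer reactions. An analyst who follows the text would still test it under the label of reactivity, and a chance difference could be reported as an autonomic effect. The same imbalance would also shift the later raw levels, because a person's resting and presentation values are correlated. Physiology is a secondary outcome, so what is at stake is the reading of the secondary results.

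**Working it through.** **1. The plan's own figures.** The article gives no sample size for physiology. Its PSAS calculation supplies the group sizes used below. With f = 0.15, m = 6, ρ = 0.50, ε = 0.50 and N = 78:

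- λ = f²·N·m·ε/(1 − ρ) = 0.0225 × 78 × 6 × 0.5/0.5 = 10.53
- df1 = (2 − 1)(6 − 1)(0.5) = 2.5; df2 = (78 − 2)(6 − 1)(0.5) = 190
- power = 0.801, and 78 is the smallest even N that reaches 0.80
- 78/0.85 = 91.8, rounded up to 92

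Both figures reproduce and neither bears on this point. Evaluable and recruited numbers per arm are 39 and 46.

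**2. What can differ at Session 1 rest.** Randomization precedes T0, so the arms already exist. Arm-specific content begins only with the interview, and participants are blinded to allocation. Under identical procedures any difference is chance. The 95% range of a chance standardized difference is ±1.96·√(2/n):

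- n = 39 per arm: 1.96 × 0.226 = 0.44
- n = 46 per arm: 1.96 × 0.209 = 0.41

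Each variable tested there at two-sided 0.05 has about a 5% chance of a false difference. Staff are not blinded, so unequal handling is possible, but that would not be an effect of interviewer reactions either.

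**3. Carry-over into raw levels.** With unit variances and correlation ρ between rest and presentation, a chance difference d at rest gives an expected presentation difference of ρ·d. For d = 0.44 this is 0.22 at ρ = 0.5 and 0.31 at ρ = 0.7. A null simulation (39 per arm, 20,000 replicates, ρ assumed) gave:

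| ρ | Level test significant, given a significant rest test | Change score significant, given a significant rest test | Change score, all trials | Rest or presentation level significant, all trials |
|---|---|---|---|---|
| 0.3 | 8% | 23% | 5.1% | 9.6% |
| 0.5 | 19% | 20% | 4.9% | 8.8% |
| 0.7 | 36% | 12% | 5.0% | 8.5% |
| 0.9 | 60% | 7% | 4.6% | 6.9% |

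Over all trials the presentation-level test alone also stays near 5% (4.7% to 5.3%). So the level test is not biased in itself. The harm is an added test that cannot be informative, and a level result that cannot be separated from an imbalance already on record.

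**4. What the baseline value offers.** Residual variances for a Session 1 level, in units of the raw variance:

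- raw level: 1
- change score: 2(1 − ρ) = 1.00 at ρ = 0.5; 0.60 at ρ = 0.7
- level adjusted for Session 1 rest: 1 − ρ² = 0.75 at ρ = 0.5; 0.51 at ρ = 0.7

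**5. Sessions 2 and 3.** Let ρ₁ be the correlation of a later presentation level with Session 1 rest, and ρ_w its correlation with rest in the same session. The own-session difference is the more precise when 2(1 − ρ_w) < 1 − ρ₁². For ρ₁ = 0.5 that means ρ_w > 1 − 0.75/2 = 0.625; for ρ₁ = 0.7, ρ_w > 1 − 0.51/2 = 0.745.

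**The case against.** The best defence is the sentence that follows the disputed phrase. The main physiological outcome is a difference from stabilization, and the habituation slopes use ΔRMSSD and ΔHR. On that reading the list of phases only names what is needed to compute reactivity, and nothing says that a resting difference at Session 1 will be reported as an effect. Much of this stands: these analyses use stabilization properly and keep their nominal error. It does not clear the text, which names stabilization as a phase compared between groups and also plans comparisons of levels. Nor can the word readily mean the exercises after the interview, which have other names throughout.

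Four stronger readings are tempting and are not supported.

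- **Stabilization in Sessions 2 and 3 is both forbidden as an outcome and compared.** The restriction concerns recordings. In that section the word may mean only the voice recordings, and standardization fits the acoustic rule under Exploratory variables. Those later rest periods also follow randomized exposure, so a difference there may be real carry-over or anticipation.
- **No physiology is recorded at T0.** The Fig. 4 caption is true of when the data are taken, since Session 1 stabilization occurs at the Session 1 visit. The mismatch is one of labels.
- **The false-positive risk at rest is 12% to 19%.** That assumes four separate tests at 0.05 (1 − 0.95⁴ = 18.5% if independent, about 12% at correlation 0.8). The article specifies no such set of tests.
- **Failing to adjust wastes the equivalent of 33% to 96% more participants.** That is 1/0.75 and 1/0.51, so it rests on assumed correlations. It also takes silence about covariates as a decision against them, although a condensed article may leave secondary models to the analysis plan.

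**Conclusion.** The point holds in a limited form. As written, the plan compares a pre-exposure T0 measurement between arms and calls it reactivity. At Session 1 that comparison cannot show a treatment effect. It carries about a 5% chance of a false difference per measure, and an imbalance there can colour the level comparisons of mean HR, RMSSD, SDNN and pNN50. Tonic skin conductance may be touched too, since it is compared over the whole intervention period without excluding stabilization.

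The conclusion assumes that both arms are handled alike up to the first interview. The variance figures assume ρ between 0.5 and 0.7, which the article does not give. ΔRMSSD, ΔHR, their slopes, the PSAS analysis and the sample size of 78 (92 recruited) are not affected. The correction is worthwhile because it is nearly free, but it concerns secondary outcomes only.

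**What to change.** - In Data preparation and planned analyses, state that the Session 1 stabilization is a baseline reference, and remove it from the phases compared between groups.
- Adjust the between-group level comparisons of mean HR, RMSSD, SDNN and pNN50 for each participant's Session 1 stabilization value of the same measure. Keep ΔRMSSD as planned.
- In the pre-session section, say whether the restriction on Session 2 and 3 recordings covers the physiological stabilization or only the voice data.
- Align the Fig. 4 caption with the T0 label.

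A separate outcome for arousal at rest before Sessions 2 and 3 would be an optional addition; the correction does not depend on it.

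The cost is a few sentences, with no new data. The one drawback is that in Sessions 2 and 3 adjustment for Session 1 rest may be less precise than the own-session difference, which is a reason to keep ΔRMSSD alongside.

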#### First session

When the VR content begins, participants first wait in a virtual waiting area where they receive entry guidance through on-screen and audio instructions. After this brief orientation, the interviewer requests a brief self-introduction. Upon receiving the question, participants are given a 20-s preparation period (indicated by an on-screen countdown timer) to organize their thoughts before beginning their response. Participants then present for 1 min while monitoring a timer interface. In the experimental group (EG) intervention, the interviewer demonstrates positive reactions such as nodding while listening to participants’ self-introductions and responds with “Yes, I heard you well.”, “Please relax and feel free to speak comfortably.” upon presentation completion. In the control group (CG), interview questions are provided through automated voice prompts, with no visual or auditory interviewer reactions provided. Both groups participate in a 2-min “positive self-talk session” immediately following presentation simulation, after which equipment is removed and questionnaire surveys are completed. Participants are scheduled to revisit the laboratory for the second session after 48 h (± 2 h). Figure 2 shows screen captures of what participants observe through VR.

**Fig. 2 Fig2:**
[figure not shown]
Actual VR screen captures as viewed by participants. **A** Situation where participants wait and receive entry guidance. **B** Face-to-face situation with the interviewer. **C** Timer interface displayed when responding to interview questions. **D** Relaxation training interface immediately following interview simulation

#### Second session

Participants undergo the same stabilization session as the first session before proceeding with the interview. In the experimental group, the interviewer requests an explanation of strengths and weaknesses with a neutral expression. Participants receive a 20-s preparation period followed by 1 min for their presentation. The interviewer maintains neutral observation of the participant before examining application materials and responding “Hmm… I see” upon presentation completion. In the control group, interview questions are provided through automated voice prompts with no visual or auditory interviewer reactions. Both groups participate in a 2-min “worry reflection and acceptance practice” immediately following presentation simulation.

#### Third session

Participants proceed with interviews following the stabilization session. In the experimental group, the interviewer displays a tired expression, sighs, makes notes on paper, and asks “Next, please tell me about the two most memorable news items you’ve seen recently and explain your reasons.” After a 20-s preparation period, participants present for 1 min. During the participant’s response, the interviewer begins whispering to another interviewer, then responds with negative expression and voice tone upon response completion: “I can’t hear your voice well, so please speak a little louder and more clearly. Also, could you explain what you mentioned in more detail?” In the control group, interview questions are provided through automated voice prompts with no visual or auditory interviewer reactions. Both groups participate in a 2-min “breathing and muscle relaxation training” immediately following presentation simulation. Across groups, the interview topics, preparation time, speaking duration, and session sequence are identical; only the interviewer reaction format differs between conditions. The positive, neutral, and negative interviewer reactions were designed as sequential components of a single graded exposure intervention rather than as separate intervention arms. Figure 3 shows the intervention process and questionnaire administration timepoints.

**Fig. 3 Fig3:**
[figure not shown]
Schematic representation of session-specific intervention components and questionnaire administration timepoints across three VR sessions. The experimental group receives graded interviewer reactions progressing from positive (Session 1) to neutral (Session 2) to negative responses (Session 3), while the control group receives automated voice prompts without visual or social-emotional interviewer reactions. Across groups, the interview structure, topics, preparation periods, and speaking durations are identical; only the interviewer reaction format differs. Each session includes specific coping strategies: positive self-talk (Session 1), worry reflection and acceptance (Session 2), and breathing/muscle relaxation techniques (Session 3). Surveys are administered at baseline (T₀) and immediately after each session (T₁, T₂, T₃), with follow-ups at 6 weeks (T₄) and 12 weeks (T₅)

#### Follow-up with open-ended questions

Both groups complete questionnaires remotely at 6 and 12 weeks following the third intervention. Questionnaires include open-ended items allowing participants to freely provide feedback on whether they experienced actual presentation situations such as classes or interviews after the intervention and, if so, in what aspects they perceived intervention effects. Figure 4 shows intervention timepoints and data collection timepoints throughout the experimental process.

**Fig. 4 Fig4:**
[figure not shown]
SPIRIT schedule of enrollment, interventions, and assessments throughout the study timeline. Timepoints are designated as follows: -T1 (online self-screening, in-person eligibility confirmation at the laboratory, written informed consent and randomization), T0 (baseline assessment), T1–T3 (immediate post-session assessments during the three VR intervention sessions), T4 (6-week follow-up), and T5 (12-week follow-up). The intervention phase (T1–T3) includes both experimental group (graded interviewer reactions) and control group (automated prompts) protocols. Primary outcomes (PSAS, LSAS-SR, FNE-B) are measured at all six timepoints, while physiological indicators (PPG, GSR) and behavioral measures (movement, voice data) are collected only during the intervention sessions (T1–T3). X marks indicate when each assessment or procedure is conducted

#### Participant timeline: schedule of enrollment, interventions, and assessments

### Outcome measurement

#### Primary outcome

Public Speaking Anxiety Scale (PSAS): The primary outcome measure is change from baseline in Korean-version PSAS total scores at each post-baseline assessment occasion (T1–T5), with assessments conducted at baseline (T0), immediately after each intervention session (T1, T2, and T3), and at 6-week (T4) and 12-week (T5) follow-ups. The PSAS is a 17-item self-report questionnaire comprising cognitive, behavioral, and physiological dimensions of public speaking anxiety [39]. The scale demonstrates good psychometric properties and is well-suited for monitoring public speaking anxiety treatment effects [40]. The primary estimand is the between-group difference in mean change from baseline in PSAS total scores across post-baseline assessment occasions, estimated using a linear mixed-effects model with fixed effects for group, assessment occasion, and their interaction.

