**Methods:**

This two-arm, parallel-group, superiority randomized controlled trial will recruit 92 Korean university students aged ≥18 years with elevated PRPSA (Personal Report of Public Speaking Anxiety-18 ≥ 58). Participants will be randomized 1:1 to receive either VR interview training with graded interviewer reactions or control VR training with automated voice prompts only. The intervention consists of three VR sessions, with assessments conducted at baseline, immediately after each session, and at 6- and 12-week follow-ups. The primary outcome is change from baseline in Public Speaking Anxiety Scale (PSAS) total scores at each post-baseline assessment occasion, analyzed using a linear mixed-effects model including fixed effects for group, assessment occasion, and their interaction. Secondary outcomes include Liebowitz Social Anxiety Scale–Self Report and Fear of Negative Evaluation–Brief scores, as well as physiological indicators reflecting anxiety responses during VR exposure, including heart rate variability and electrodermal activity. Exploratory analyses will examine behavioral synchrony using motion energy analysis of video recordings and acoustic features of speech to capture anxiety-related movement and vocal patterns.

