### Sample size

The primary outcome is public speaking anxiety as measured by the PSAS, assessed at six prespecified assessment occasions (baseline; immediately after each of the 3 sessions; 6- and 12-week follow-ups). The study is powered to detect a group-by-assessment-occasion interaction reflecting between-group differences in change from baseline in PSAS across repeated assessments.

Previous meta-analyses demonstrate that VRET produces large effects versus waitlist conditions (*g* = 0.90) and shows comparable efficacy to in vivo exposure therapy [16, 34]. However, since both groups in the present trial receive active PSA training, we anticipated only a small incremental effect. Our intervention extends standard VR exposure by introducing graded interviewer reactions delivered as sequential components of a single exposure package. Research indicates that social-evaluative characteristics of virtual audiences can influence performance confidence and anxiety responses, with some improvements transferring to real-world public speaking performance [25, 34].

Based on these findings, a conservative effect size of *f* = 0.15 was assumed for between-group differences in repeated outcome change. A priori power analysis using G*Power (ANOVA: repeated-measures, within-between interaction; *α* = 0.05, 1 − β = 0.80, two groups, six measurements, correlation among repeated measures = 0.50, nonsphericity correction *ε* = 0.50) indicated a total sample of *N* = 78. Although the primary analysis will use a linear mixed-effects model, the sample size was calculated using a repeated-measures ANOVA framework focusing on the group-by-assessment-occasion interaction. This interaction corresponds to the primary estimand of interest and aligns with the primary analysis model. The ANOVA-based approach was adopted as an approximation because prior data were insufficient to parameterize variance components required for LMM-based simulation. To account for approximately 15% attrition commonly observed in VR exposure studies [35], the recruitment target was set at 92 participants (46 per group). Figure 1 shows the CONSORT flow diagram for the recruitment process.

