#### Secondary outcomes

Liebowitz Social Anxiety Scale-Self Report (LSAS-SR): Used to measure social anxiety which is highly related to public speaking anxiety. LSAS-SR is a 48-item scale assessing anxiety and avoidance levels across 24 social situations, with the Korean version validated for university students [41]. The scale demonstrates excellent internal consistency (*α* = 0.92–0.95) [41]. LSAS-SR total scores will be summarized at the group level and compared across the same six assessment occasions used for the primary outcome (T0–T5). 

Fear of Negative Evaluation-Brief (FNE-B): A 12-item scale measuring fear of negative evaluation. Originally developed by Watson and Friend (1969) and shortened by Leary (1983) [42], the Korean version was validated by Lee and Choi (1997) [43]. Items are rated on a 5-point Likert scale, with higher scores indicating greater fear of negative evaluation [44]. FNE-B total scores will be summarized at the group level and compared across the same six assessment occasions used for the primary outcome (T0–T5). 

Physiological indicators: To objectively compare short-term anxiety induction levels and long-term desensitization patterns between groups during exposure, photoplethysmography (PPG) for heart rate measurement and galvanic skin response (GSR) measurement are implemented [45]. For cardiac autonomic activity, the principal variables will include RMSSD and SDNN (log-transformed if distributional assumptions are violated), and pNN50, derived from PPG signals collected from the earlobe at 256 Hz. For electrodermal activity, the principal variables will include mean tonic skin conductance level (SCL) and phasic SCR peak amplitude and peak count derived from GSR signals collected from the index and middle fingers of the non-dominant hand at 256 Hz. These participant-level physiological variables will be summarized by session and compared between groups across intervention stages. Signals will be processed using third-order Savitzky-Golay filters to preserve signal strength while providing smoothing [46]. Heart rate variability reflects autonomic nervous system responses to stress and anxiety [47], while galvanic skin response serves as an indicator of sympathetic nervous system arousal levels [48].

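### The primary outcome is defined as five changes from baseline but sized as six PSAS measurements; if change scores are what is fitted, the interaction tested is not the one that was powered.

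*Protocol article*

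**What the plan says.** The protocol article describes the primary endpoint in two ways.

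- **Five changes.** The Primary outcome section states "The primary outcome measure is change from baseline in Korean-version PSAS total scores at each post-baseline assessment occasion (T1–T5"). The abstract (Methods) gives the same outcome and names its model in the same sentence: "change from baseline in Public Speaking Anxiety Scale (PSAS) total scores at each post-baseline assessment occasion, analyzed using a linear mixed-effects model", with fixed effects for group, occasion and their interaction. The estimand is worded to match: "The primary estimand is the between-group difference in mean change from baseline in PSAS total scores across post-baseline assessment occasions".
- **Six measurements.** The Sample size section describes the outcome as PSAS "assessed at six prespecified assessment occasions (baseline; immediately after each of the 3 sessions; 6- and 12-week follow-ups"), and its G*Power inputs include "two groups, six measurements, correlation among repeated measures = 0.50". The Secondary outcomes section says that the secondary scales are "compared across the same six assessment occasions used for the primary outcome (T0–T5").

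The Sample size section adds: "The study is powered to detect a group-by-assessment-occasion interaction reflecting between-group differences in change from baseline in PSAS across repeated assessments". It then says that this interaction matches both the primary estimand and the primary model. Data preparation and planned analyses lists the fixed effects and participant random effects, but does not say whether the response is the raw score or the change, or whether T0 is one of the occasions.

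**The concern.** The two descriptions give different interaction tests under the same name.

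- With raw PSAS as the response and T0 as a level, the group-by-occasion interaction has (2 − 1)(6 − 1) = 5 degrees of freedom. It contains every between-group difference in change from baseline.
- With change from T0 as the response, baseline has been subtracted out. The interaction has (2 − 1)(5 − 1) = 4 degrees of freedom and asks only whether the group difference varies among T1–T5. A benefit that appears after the first session and then holds steady falls wholly into the group main effect.

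This matters because the interaction is what the trial is powered on, and the Discussion treats a significant interaction as the evidence of greater anxiety reduction. If change scores were fitted, a sustained benefit could leave that test null, and the quoted 80% would belong to another test.

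**Working it through.** **Inputs (Sample size section):** f = 0.15, alpha = 0.05, power 0.80, k = 2 groups, m = 6 measurements, correlation rho = 0.50, nonsphericity epsilon = 0.50, N = 78, attrition 15%, target 92.

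**Formula** (G*Power, repeated measures, within-between interaction), with power taken from the noncentral F distribution:

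- lambda = f² × N × m × epsilon / (1 − rho)
- df1 = (k − 1)(m − 1) × epsilon
- df2 = (N − k)(m − 1) × epsilon

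**1. The plan's own figure, m = 6.**
- lambda = 0.0225 × 78 × 6 × 0.50 / 0.50 = 10.53; df1 = 5 × 0.50 = 2.5; df2 = 76 × 5 × 0.50 = 190.
- Power = 0.801 at N = 78 (0.790 at N = 76).
- 78 / 0.85 = 91.8, rounded up to 92.

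Both stated figures reproduce, so the trial was sized with T0 as a level.

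**2. Five change scores, m = 5, other inputs carried over.** If the repeated measures have common variance and correlation 0.50, each change score has variance 2(1 − 0.50) = 1 times the original, and two change scores correlate 0.50. The standard deviation and rho therefore carry over.
- lambda = 0.0225 × 78 × 5 × 0.50 / 0.50 = 8.775; df1 = 4 × 0.50 = 2; df2 = 76 × 4 × 0.50 = 152.
- Power = 0.751 at N = 78.
- 80% needs N = 88 analysed (0.804; 0.794 at N = 86). 88 / 0.85 = 103.5, so 104 recruited.

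**3. Sensitivity to epsilon, m = 5, f = 0.15, N = 78.**

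| epsilon | power |
|---|---|
| 0.50 | 0.751 |
| 0.55 | 0.780 |
| 0.60 | 0.806 |
| 0.625 | 0.819 |

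**4. Sensitivity to the shape of the effect.** Step 2 keeps f = 0.15 after a level is dropped, but f itself depends on which occasions are counted. The protocol states no effect pattern, so the patterns below are illustrative assumptions. With two equal groups, f = SD of the group differences over the occasions / 2, in units of the outcome SD. Each pattern is scaled so that this SD over T0–T5 is 0.30 (f = 0.15, six-level power 0.801). f is then recomputed over T1–T5 and put into the m = 5 formula at epsilon = 0.50, N = 78.

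| Group difference at T0, T1, …, T5 (relative) | f over T1–T5 | Power, T1–T5 interaction |
|---|---|---|
| 0,1,1,1,1,1 (constant from T1) | 0 | 0.05 |
| 0,1,2,3,3,3 (rise, then plateau) | 0.104 | 0.43 |
| 0,1,2,3,2,1 (peak at T3, then fade) | 0.117 | 0.53 |
| 0,1,2,3,4,5 (linear by occasion) | 0.124 | 0.58 |
| 0,0,0,1,1,1 (from T3 only) | 0.147 | 0.73 |
| 0,0,0,0,1,1 (follow-up only) | 0.156 | 0.78 |

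**5. Check by simulation.** 4,000 runs with N = 78, correlation 0.50 throughout and a multivariate interaction test under the constant-from-T1 pattern gave 94.6% rejection for the T0–T5 interaction and 4.9% for the T1–T5 change-score interaction. The first figure exceeds 0.801 because the simulation has no nonsphericity. The second is the alpha level, as expected.

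**The case against.** The strongest reply is that a coherent reading exists. An interaction that reflects change from baseline, as the Sample size section words it, needs T0 as a level. The analysis section gives one model for all questionnaire outcomes, and the Secondary outcomes section places those at T0–T5. The Discussion's use of the interaction also needs T0 in the model. Reporting change as the metric while estimating it as contrasts from a raw-score model is ordinary practice, and five contrasts from six measurements are no contradiction. On that reading six measurements is right and 80% stands. This part of the reply holds. A reader might infer from the two descriptions that the trial is underpowered or the sample size miscalculated. The document does not support that: 78 and 92 are both correct for the inputs given.

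The size of any shortfall is also soft. Epsilon need not stay at 0.50 when a level is dropped, the effect patterns are not the protocol's, and the protocol calls its ANOVA calculation an approximation. A mixed model also uses partial data from dropouts; if all 92 contributed fully, the five-measurement power would be 0.823 at epsilon = 0.50. In addition, under a change-score model the stated estimand would more naturally be the averaged group effect, to which the interaction powers above do not apply. These points limit what can be claimed for the 75%.

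They do not remove the conflict. The abstract attaches the model to the change outcome, the analysis section does not correct it, and the Sample size section asserts that calculation and model agree. Details left to an analysis plan would not make these statements consistent.

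**Conclusion.** The point holds in conditional form. The article defines its primary response in two ways and nowhere settles which is fitted.

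- **If raw PSAS at T0–T5 is the response,** the sizing matches the model and the stated 80% at N = 78 reproduces (0.801).
- **If change from baseline at T1–T5 is the response,** as the abstract literally says, the interaction has no power beyond alpha against a group difference that is constant from T1. It is not the interaction that was sized, and the claimed agreement between calculation and model fails. Its power at N = 78 is about 75% with the plan's f, correlation and epsilon carried over.

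The loss of the baseline contrast follows from the structure of the model and needs no numerical assumption. The 75% does: it rests on f = 0.15 and epsilon = 0.50 applying unchanged to five occasions, and on 78 analysed. It rises to about 81% at epsilon = 0.60, and ranges from 0.05 to 0.78 over the illustrative patterns.

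**What to change.** Use one definition in the abstract, Sample size, Primary outcome, Secondary outcomes and Data preparation and planned analyses: the response is the PSAS total score at all six occasions, T0 is a level of assessment occasion, and the changes from T0 at T1–T5 are estimated as group-by-occasion contrasts from that model. The existing calculation then matches the fitted model. The cost is a few sentences, with no new data, no further participants and no change to 78 or 92.

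If change scores are kept as the response, set the number of measurements to five, restate the interaction's power at N = 78 as about 75% under the plan's inputs, and say that this interaction does not capture a difference that is constant from T1. The cost is then a less favourable stated power.
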